## Abstract

**Background:**

Surgical site infections (SSIs) are among the most common hospital acquired infections. While the incidence of SSI in certain indicator procedures is the subject of ongoing surveillance efforts in hospitals and health care systems around the world, SSI rates vary markedly within surgical categories and are poorly represented by routinely monitored indicator procedures (eg, mastectomy or hernia surgery). Therefore, relying on indicator procedures to estimate the burden of SSI is imprecise and introduces bias as hospitals may take special precautions to achieve lower SSI rates. The most common cause of SSI is *Staphylococcus aureus* (*S. aureus*), as recently confirmed by a Europe-wide point-prevalence study conducted by the European Centre for Disease Prevention and Control (ECDC).

**Objective:**

The primary objective of this study is to determine the overall and procedure-specific incidence of *S. aureus* SSI in Europe. Secondary objectives are the overall and procedure-specific outcomes as well as the economic burden of *S. aureus* SSI in Europe. Explorative objectives are to characterize the composition of the surgical patient population and to estimate the number of patients at risk for *S. aureus* SSI.

**Methods:**

A retrospective, multinational, multicenter cohort study (*Staphylococcus aureus* Surgical Site Infection Multinational Epidemiology in Europe [SALT] study) with a nested case-control part will be conducted. The study will include all surgical procedures at a participating center in order to prevent selection bias and strengthen the understanding of SSI risk by determining the incidence for all common surgical procedures. Data will be assessed in the cohort population, including 150,000 adult patients who underwent any surgical procedure in 2016, and the case-control population. We will match patients establishing *S. aureus* SSI 1:1 with controls from the same center. Data on demographics, surgery, and microbiology will be exported from electronic files. More detailed data will be captured from the case-control population. The SALT study will include 13 major or academic surgical centers in Europe, comprising 3 in France, 4 in Germany, 2 in Italy, 3 in Spain, and 1 in the United Kingdom. Sites were selected using a feasibility questionnaire.

**Results:**

The SALT study is currently recruiting patients. The aim is to complete recruitment in February 2018 and to close the database in September 2018. The final results are expected by the end of 2018.

**Conclusions:**

Results of the SALT study will help to better understand the precise risk of certain procedures. They will also provide insight into the overall and procedure-specific incidence and outcome as well as the economic burden of *S. aureus* SSI in Europe. Findings of the study may help guide the design of clinical trials for *S. aureus* vaccines.

**Trial Registration:**

ClinicalTrials.gov NCT03353532; https://clinicaltrials.gov/ct2/show/NCT03353532 (Archived by WebCite at http://www.webcitation.org/6xAK3gVmO)

## Introduction

### Background

Surgical site infections (SSIs) are among the most common hospital acquired infections and constitute an important quality criterion in health research [1,2]. The incidence of SSIs in certain indicator procedures is the subject of ongoing surveillance efforts in hospitals and health care systems around the world [1,3,4]. However, SSI rates vary markedly within surgical categories and are poorly represented by routinely monitored indicator procedures such as mastectomy, upper limb amputation, or inguinal hernia surgery [4]. Therefore, relying on indicator procedures to estimate the overall burden of SSIs is imprecise and introduces bias as hospitals may take special precautions to achieve lower SSI rates in indicator procedures. *Staphylococcus aureus* (*S. aureus*) is the most common cause of SSIs, as recently confirmed by a Europe-wide point-prevalence study conducted by the European Centre for Disease Prevention and Control (ECDC) [5].

Treatment of *S. aureus* infections is challenging due to the emergence of multi-drug resistant strains such as methicillin-resistant *S. aureus* (MRSA). To better plan future trials on new treatment strategies, knowledge on incidence and risk factors is of utmost importance.

Currently available data suggest that while the overall SSI rate and the proportion of SSIs caused by *S. aureus* vary, the absolute *S. aureus* SSI rate is similar for different procedures. Focusing on *S. aureus* SSIs, we aim to demonstrate that the *S. aureus* SSI rate is independent of the procedure performed and rather a consequence of cutaneous incisions. Such a demonstration would amount to a paradigm shift and allow future prevention studies to proceed differently.

SSIs are associated with poor outcome, prolonged hospitalization, and increased treatment costs [6]. Estimated excess treatment costs range between US $ 1000 to $20,000 [6-10]. Treatment costs depend, among other factors, on the depth of SSI (superficial, deep, or organ space) and the prior surgical procedure. However, the exact treatment costs remain unknown, as previous estimates are based on limited data from single institutions [9], provider networks [11], or highly aggregated data from surveillance programs [7]. Due to this heterogeneous data source, prior cost estimates for Europe show a wide range of results [12].

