#### Sample Size

We assume a 1.5% incidence rate of *S. aureus* SSI. Incidence rates can be determined with a 95% CI of plus or minus 0.5% by observing 1500 surgical procedures, assuming a mean *S. aureus* SSI rate of 1%. Lower incidence rates would result in smaller 95% CIs with a similar sample size or similar CIs with a smaller sample size. Therefore, at least 15 centers should be included in the analysis, resulting in 90,000 to 150,000 patients observed patients. This will allow us to calculate incidence rates with meaningful precision for all surgical procedures performed on at least 1% to 1.5% of respective patients. To further broaden the scope of this study, 1 or 2 centers per country will be included specializing in types of surgery not traditionally performed at academic surgical centers but highly relevant to the prevention of SSI in otherwise healthy patients (eg, plastic surgery). Assuming a 1.5% incidence rate of *S. aureus* SSI, in a population of 150,000, 2250 cases will be matched to 2250 controls.

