#### Data Collection

##### Cohort

The following variables will be collected from EHRs for descriptive purpose only: (1) age by category; (2) sex; (3) BMI; (4) comorbidities (International Statistical Classification of Diseases and Related Health Problems [ICD-10] codes); (5) diabetes; (6) type of procedure; (7) duration of procedure; (8) occurrence of SSI related to observed procedure within 90 days, including date of diagnosis; (9) wound class.

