### Statistical Analysis

Assuming a mean *S. aureus* SSI rate of 1% [5], incidence rates can be determined with a 95% CI of plus or minus 0.5% by observing 1500 surgical procedures. Therefore, at least 15 centers will be included in the analysis, resulting in 90,000 to 150,000 observed patients. Assuming an incidence rate of *S. aureus* SSI of 1.5% in a population of 150,000, 2250 cases will be matched to 2250 controls.

Data will first be analyzed for missing values. We will perform a qualified evaluation of missingness mechanisms for each variable with more than 1% missing values. In case data are missing completely at random, patients with the missing value will be excluded from that respective analysis step (complete record analysis). For values not missing at random, multiple imputation using chained equations will be performed and compared to a complete record analysis for improved robustness of results. We will perform in-depth descriptive statistics of all parameters observed. Country-based and institution-based incidence rates will be determined for each procedure (eg, ventral hernia repair) and each category (eg, vascular surgery). For each incidence rate, the 95% CIs for a binominal proportion will be calculated. Costs will be calculated for both procedures and categories. Accounting for the usually non-normal distribution of costs in medical settings, statistical analyses (eg, CI construction) will be carried out using non-parametric bootstrap procedures. Reported SSI rates and cost will be further stratified by depth of SSI (eg, superficial, deep). Association between major cost drivers and SSI occurrence, as well as overall costs and SSI occurrence, will be determined using bootstrapped t tests.

Multivariable regression analysis will be used to confirm significance of SSI occurrence for overall treatment costs.

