#### Primary Analysis

The primary objective of this study is to determine the overall and procedure-specific incidence of *S. aureus* SSI in Europe. The primary analysis will consist of calculating the incidence using 95% CIs.

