#### Further Statistical Evaluation

Distribution of data within groups will be described using count, percentage, or valid n, mean, standard deviation and percentiles (0, 25, 50, 75, and 100) as appropriate. CIs (level 95%) will be calculated to aid interpretation. Sensitivity analyses will include further multiple regression approaches (eg, Poisson regression for rates).

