With SSI rates being the primary endpoint, SSI detection methodology is crucial in this study. Prior studies and surveillance effort, if specifying detection methodology at all, are usually limited to the analysis of administrative code data [14,15]. However, a recent publication demonstrated that using bacteriological data is superior and combining both—administrative and bacteriological data—could be even more advantageous [16]. In this very study, the detection by means of bacteriologic data will result in high sensitivity, specificity, and negative predictive values (96.4%, 91.4%, and 99.9%, respectively) for deep SSI with no significant difference to the use of both types of data.

Cases are matched 1:1 to controls within each center by software provided by the coordinating center. Matching cases and controls within centers addresses the need for risk-adjustment to institutional characteristics and practices. Cases are matched to controls that received the same type of procedure. Individual pair-wise matching will be used, utilizing optimal matching to ensure the overall smallest possible Euclidean distance between cases and controls. Acknowledging the limited utility of using the National Healthcare Safety Network (NHSN) risk index, which only accounts for the existence of certain risk factors but not their composition, a propensity score is determined by logistic regression.

Costs are calculated by multiplication of the per-unit price for major cost drivers with the number of units used. Minor cost drivers, such as drug use, will be disregarded, as length of stay has been repeatedly shown to account for 90% of excess SSI costs [11].

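### The Background aims to demonstrate that the S. aureus SSI rate does not depend on the procedure, but no objective carries this aim and separate confidence intervals per procedure cannot demonstrate it

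*Protocol article*

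**What the plan says.** In the Introduction (Background), the article states the aim of demonstrating that the S. aureus "SSI rate is independent of the procedure performed and rather a consequence of cutaneous incisions". It adds: "Such a demonstration would amount to a paradigm shift and allow future prevention studies to proceed differently".

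The Objectives section lists primary, secondary and exploratory objectives. They determine, characterize or estimate quantities; none concerns independence from procedure.

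The analysis text matches those objectives:

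- Primary Analysis: "The primary analysis will consist of calculating the incidence using 95% CIs".
- Statistical Analysis: "For each incidence rate, the 95% CIs for a binominal proportion will be calculated".
- Data Collection, Cohort, introducing a list that includes type of procedure: "The following variables will be collected from EHRs for descriptive purpose only".
- Further Statistical Evaluation: "Sensitivity analyses will include further multiple regression approaches (eg, Poisson regression for rates"). No comparison of procedures is mentioned.
- Discussion, Principal Findings, on the nested part: "Cases are matched to controls that received the same type of procedure".

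Sample Size rests on the interval width of a single rate: 1,500 procedures for ±0.5% at a rate of 1%.

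**The concern.** Demonstrating that a rate does not depend on procedure means bounding how far procedures differ. That needs a measure of between-procedure variation and a limit for what counts as alike. The article states neither, and its incidence analysis treats each procedure on its own. Failing to see a difference, whether through overlapping intervals or a non-significant term, is not evidence of equal rates.

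At stake is the article's most far-reaching statement, since the Background says the demonstration would change how prevention studies proceed. The same section already says that available data suggest similar absolute rates across procedures, so imprecise results could easily be taken as confirmation.

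**Working it through.** **1. The passages side by side.** The Background sets a no-difference aim. The Objectives omit it. Statistical Analysis and Primary Analysis give one interval per rate. The cohort variables are labelled descriptive. Cases and controls share the same procedure type by matching, so the nested part cannot estimate a procedure effect. No stated analysis leads to the Background aim.

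**2. The plan's own precision figure.** Inputs from Sample Size: p = 0.01, n = 1,500.

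- Wald half-width = 1.96 × √(p(1−p)/n) = 1.96 × √(0.01 × 0.99/1500) = 0.00504, or ±0.50 points.
- n for exactly ±0.5 points = 1.96² × 0.0099/0.005² ≈ 1,521, rounded up to 1,522.

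The stated figure reproduces.

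**3. What one interval leaves open.** The exact (Clopper-Pearson) 95% interval for 15/1500 is 0.56% to 1.64%. The ratio of its ends is 1.64/0.56 ≈ 2.9.

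**4. What a contrast of two procedures leaves open.** With 1,500 in each:

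- SE of the difference at 1% = √(2 × 0.01 × 0.99/1500) = 0.00363.
- 95% half-width = 1.96 × 0.00363 = 0.0071, or ±0.71 points around a 1% rate.
- Sample Size also says "We assume a 1.5% incidence rate of" S. aureus SSI. At 1.5% the half-width is 1.96 × √(2 × 0.015 × 0.985/1500) = 0.0087, or ±0.87 points.

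**5. Overlap is uninformative at this size.** Wilson intervals at n = 1,500 are 0.61% to 1.64% for an observed 1.0%, and 1.40% to 2.84% for an observed 2.0%. They overlap although one rate is twice the other. A two-proportion test (pooled null variance, two-sided 5%) has power 23% for 1.0% vs 1.5% and 62% for 1.0% vs 2.0%. These figures concern one pair at the minimum size. They show why reading intervals against each other fails, not what the whole cohort could detect.

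**6. What a joint analysis could detect.** The article does not give the number of procedures reaching 1,500, so I assume 20, 60 or 100; at 1,500 each, 90,000 to 150,000 patients allow at most 60 to 100. With half the procedures at 0.8% and half at 1.2%, each deviates by 0.002 from the 1% mean. The noncentrality of a chi-square heterogeneity test is k × 1500 × 0.002²/(0.01 × 0.99) = 0.606k.

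| Procedures (k) | Noncentrality | Power at 5% |
|---|---|---|
| 20 | 12.1 | about 50% |
| 60 | 36.4 | about 86% |
| 100 | 60.6 | about 97% |

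If log rates instead vary with SD 0.3, the central 95% of true rates spans a ratio of exp(2 × 1.96 × 0.3) = 3.2. Simulated power is then about 83% with 20 procedures and over 99% with 60. Centre effects are ignored throughout. So the cohort may well be able to quantify variation between procedures, but only if it is analysed jointly.

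**The case against.** The strongest reply is that the sentence stands only in the Background. The Objectives ask for procedure-specific incidence, the primary analysis delivers that, and neither Conclusions section repeats the independence claim. This stands, and it limits the point: the primary objective and its analysis agree with each other. But the sentence is worded as something the study aims to demonstrate, and its consequence is spelled out. If it is only motivation, rewording it costs nothing.

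Second, intervals per procedure are not the only modelling of rates, because Poisson regression is mentioned, and an unseen analysis plan may say how procedure enters it. That is fair, and lack of model detail is not the complaint. The complaint is that the article's stated aim does not match the objectives and analysis it fixes. A non-significant procedure term, with no limit fixed in advance, would not show independence either.

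Third, a reader might infer that overlapping intervals will be taken as proof of independence, or that later trials will pool procedures on that basis. The documents do not support this. No section gives an overlap rule, and the article says only that findings may help in designing vaccine trials.

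Fourth, a reader might take the 23% pairwise power as the power of the study, or assume centre clustering must lower it. Neither follows. 1,500 is the size for the stated precision and commoner procedures will have more; many procedures can be compared jointly; and an effect shared by all procedures within a centre largely cancels in a within-centre contrast.

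**Conclusion.** The point holds as a mismatch between a stated aim and the stated objectives and analysis. As written, the article has no analysis that could support the claim that the S. aureus SSI rate is independent of procedure. At its design point each procedure's interval covers roughly a threefold range, and a difference between two procedures is known only to about ±0.7 points at a 1% rate. These figures assume exactly 1,500 per procedure and independent observations. The incidence estimates and the primary objective are untouched. It is worth correcting because the far-reaching conclusion in the Background depends on this aim alone.

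**What to change.** Choose one of two changes.

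1. **Reword the Background sentence** to a descriptive aim, namely to describe how the S. aureus SSI rate varies across procedures, and make no independence claim. This changes text only.
2. **Keep the aim and add one cohort analysis of between-procedure heterogeneity**, for example a mixed logistic model with random effects for procedure and centre. Report the between-procedure SD with its confidence interval and the prediction interval of procedure rates.

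Under the second option, any conclusion that rates are similar should be judged against a limit fixed in advance and justified, on a ratio or absolute scale. The plan's ±0.5-point figure should not be reused as that limit: it describes sampling precision, and around a 1% rate it would accept 0.5% to 1.5%, a threefold spread. The main model should not adjust for features of the procedure itself, such as duration and wound class, because that changes the question.

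The cost is a little more analysis. Procedure type and SSI occurrence are already on the cohort list, although the Rationale lets single items be waived at some centres, so availability should be confirmed. The downside is that the independence claim may turn out not to be supported.

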### Rationale

Active, prospective SSI surveillance lowers SSI rates [13]; therefore, unbiased SSI rates should be determined by retrospective, non-interventional studies. This cohort study will sample a large percentage of the surgical population and thereby generate representative data. For the selection process and documentation of the overall cohort, we will limit data items to those that are generally available in electronic form, thus facilitating the sampling of an adequately sized and complete cohort with comparably low effort. Feasibility analysis of candidate study centers will assess center capability for electronic data provision. If needed, single data items may be waivered during the selection process. In this case, these data items would instead be documented as part of the nested case-control study.

The nested case-control part of this study is necessary to generate data required for outcomes and cost analyses, as most centers will not have electronic records sufficiently detailed to allow this analysis for the whole cohort. The approach avoids bias that has been introduced, for example by relying on reimbursement data to estimate costs [14], and thus describing the SSI price rather than its cost. Therefore, the best possible approach to an accurate, precise cost analysis is manual documentation by on-site medical personnel (eg, study nurses). Documentation must comprise relevant cost drivers of SSI cases and well-matched controls to allow analyses of incremental costs caused by SSI. On-site medical personnel would receive appropriate electronic case report form (eCRF) training prior to commencing documentation. In addition, manual data capturing allows concomitant plausibility checking.

Nesting the case-control study within a cohort ensures generalizability of the case-control results to the respective center as well as the cohort and, by means of a representative cohort, to the overall surgical population in Europe.

### Objectives

#### Primary Objectives

The primary objectives of this study are (1) to determine the overall incidence of *S. aureus* SSIs in Europe; and (2) to determine procedure-specific incidence of *S. aureus* SSIs in Europe.

#### Secondary Objectives

The secondary objectives of this study are (1) to determine the overall outcomes of *S. aureus* surgical SSIs in Europe; (2) to determine the procedure-specific outcomes of *S. aureus* SSIs in Europe; (3) to determine the overall economic burden of *S. aureus* SSIs in Europe; and (4) to determine the procedure-specific economic burden of *S. aureus* SSIs in Europe.

#### Exploratory Objectives

The exploratory objectives of the study are (1) to characterize the composition of the surgical patient population in Europe; (2) to estimate the number of patients at risk for *S. aureus* SSIs; and (3) to estimate the economic burden, including direct treatment and indirect costs, imposed by *S. aureus* SSIs in Europe.

## Methods

### Study Design

This is a retrospective, multinational, multicenter cohort study with a nested case-control. The study includes all surgical procedures at a participating center in order to prevent selection bias and strengthen the understanding of SSI risk by determining incidence for all common surgical procedures. Furthermore, the study will analyze the risk composition of the surgical patient population to enable the calculation of the number of patients at risk in the overall surgical population in Europe.

#### Retrospective Record

Data from all patients undergoing any surgical procedure—minimal invasive biopsies and eye surgery excluded—will be collected retrospectively. Collection will be performed by surveying electronic health records (EHRs) and databases from all participating sites (Figure 1).

Administrative and microbiological data will be accumulated to identify the target population.

#### Nested Case-Control Design

The nested case-control study generates data for analyzing costs and outcomes. Participants acquiring *S. aureus* SSIs will be documented in an electronic database and matched 1:1 to controls within each center. Criteria for matching are similar epidemiological data and procedure type, but without SSI and are specified in the Data Collection section.

